# Administrative Information

## Trial Name:

Does exercise influence burn induced inflammation?

## Trial Registration

ACTRN12620000237987p

## Protocol Version / Date

V1 160819

## Project Record Number

RGS0000003381

## Funding Sources

Fiona Wood Foundation $70,000.00

## Role of funding bodies

The funder, FWF, remains at arm’s length and have no specific input or authority over the following activities which remain the responsibility of the study investigators: study design; collection, management analysis and interpretation of data; writing of the report or decision to submit for publication.

# Introduction

Participants with a ≥ 5%TBSA burn injury, ≥ 1year after burn injury will be recruited. All patient demographic (gender, age, PMHx); injury or intervention (surgical procedures); and system (LOS, complications) co-variates will be recorded at recruitment.
The primary aim of the study will be to longitudinally analyse the effect a 6-week pulse of exercise has on the level of inflammatory biomarkers including TNF alpha and a multiplex of other cytokines at different times frames after burn. A randomised cross-over trial will be conducted with participants randomised to either an exercise or control condition in the first phase. In the second phase participants will cross over into the alternate condition e.g phase 1 exercise condition participants will change over to the control condition in phase 2. Outcome measurement and blood sampling time points will be pre-intervention, at 3 weeks after commencement of intervention/control and then at 6 weeks (completion of study period 1). These will then be repeated in study period 2 at the same time points.

Burn trauma is one of the top five causes of injury across the globe. It is undeniable that burn and trauma survivors endure temporary and permanent disabilities (1). The health, work productivity and patient costs due to transient and long term impairments are enormous and complex to quantify (WHO Report, pg7) (2, 3). Further, uniquely identifiable, a burn injury changes the life trajectory of survivors by a mechanism, as yet, to be clearly understood (4, 5). After burn, a prolonged and extreme inflammatory, catabolic response occurs (6, 7). The inflammatory load after burn injury is implicated as the primary driver of increased risk of mortality (8); systemic diseases (9, 10) and cancer (11). However, not only burn but also non-burn injury is now linked to development of, and hospitalisation for cardiovascular disease and diabetes (12, 13). The common feature that challenges the acute and long-term immune function and physical recovery after bodily injury is the inflammatory load. The interactions of inflammatory and immune biomarkers with meaningful health recovery measures have never been quantified. Due to the development of the Australian National Phenomics Centre (ANPC) on the site of Harry Perkins Institute (co-located with Fiona Stanley Hospital), we are in a position to handle and hold on to samples than ever possible.

Immune Response to Injury

We plan to facilitate an analysis of the systemic pathophysiology of the patient after burn injury with specific reference to inflammation and to understand the role of exercise after burn injury measured using biochemical, haematological and cellular responses over time.

## Primary Objective

The primary objective of this trial is to determine if exercise alters inflammation after burn injury as measured by inflammatory biomarkers (primarily TNFα) across time.

## Trial Design

This clinical trial is a single-centre, cross-sectional, crossover study designed to examine if the inflammation is altered by a pulse of exercise applied as the intervention. We hypothesise a pulse of exercise will reduce long term inflammatory load after burn injury. Participants, from each year group (time after injury - 1-3 yrs, 3-5yrs, > 5yrs (± 3 months)), will be block randomised by year after burn to either the exercise or control condition in the first study period. The exercise intervention group will complete a six-week gym program including both resistance and aerobic exercise, three days per week.

# Methods: Participants, interventions and outcomes

## **Study Setting**

The study will be conducted in the State Adult Burns Unit outpatient gym at Fiona Stanley Hospital with some exercise sessions being undertaken at participant’s local gym.

## Eligibility Criteria

Participants that meet the inclusion criteria will be identified and recruited from the SABU database. All patient demographic (gender, age, PMHx); injury or intervention (surgical procedures); and system (LOS, complications) co-variates will be recorded at recruitment.

*Inclusion Criteria*

- ≥ 5%TBSA burn injury
- Time post injury ≥ 1 year
- Male or female, ≥ 18 years old
- Satisfactory self-described health status (excluding burn injury)
- Subject understands the proposed project, is able to consent to participation

Exclusion Criteria

- Acquired or pre-existing neurological injury or disease conditions which influence the capacity to complete future exercise or walking program eg nerve injury or multi-trauma; spinal cord injury, CVA / central nervous system lesions; Patients with no fixed address.
- Unstable cardiac conditions
- Intellectually challenged patients
- Non – English speaking
- Pregnant Women
- Cancer

## Study Interventions

Control condition: The control group will be asked to continue on with normal daily tasks and their normal activity levels, monitored by activity trackers. Participants will participate in the same 6-week intervention condition (cross over study).

Exercise Intervention condition: These participants will train three times per week for six weeks either in a supervised exercise session (18 sessions) at FSH or at their local gym. The sessions will last ~60 minutes including warm up, resistance exercises, cardiovascular exercise and cool down periods. Sessions will begin with a 5-minute dynamic warm up at a light-moderate intensity equating to an RPE of 11-12 on the Borg Scale. The aerobic warm up modality will vary from session to session and include the use of treadmill and cycle ergometers. Participants will be instructed to complete an equal amount of sessions on each of these. Participants will then move into 20 minutes of aerobic exercise (AE) utilizing a variety of exercise modes and equipment. Intensity for the AE will be prescribed at 70-90% of age predicted HR max with the average HR recorded at the end of each aerobic session. The resistance training (RT) regime will consist of six exercises targeting upper and lower major muscle groups. This intervention has been used previously in a large scale clinical population study (36, 37). The RT intensity will be set at 3 sets of 10 repetitions. The resistance exercises will be progressive in nature whereby if a participant can perform an additional 2 repetitions in the final set for 2 consecutive sessions, the resistance will be increased by 5%. This progressive overload approach is widely used in resistance training programming to maximize the level of adaptation (38). The session will conclude with a 5-minute cool down period incorporating low level aerobic activities and stretching. In addition to the gym sessions, participants will be requested to perform an additional 90 minutes of home-based moderate intensity aerobic exercise (in the form of walking). The combination of 60 minutes gym based aerobic exercise and 90 minutes home based aerobic exercise is designed to meet with ACSM/AHA association guidelines of 150 minutes aerobic exercise per week (39). This exercise regime has been designed to elicit the optimal cardiorespiratory and neuromuscular response in the 6-week time-frame allocated whilst maximizing adherence and retention. An accredited Physiotherapist will be responsible for each supervised exercise session. For participants to undertake exercise sessions at their local gym they will need to be assessed as ‘low risk of adverse events to exercise’. This will be determined by an adult pre-exercise risk stratification assessment which is the Patient Health (APOC) questionnaire.

Feasibility*:* Participants undertaking exercises at their local gym will be, required to attend FSH at least once per week to enable appropriate progression of their exercises. Where this is not possible they will need to make contact with the supervising physiotherapist via phone to support appropriate progression of their exercise program at least weekly. The free Physitrack app will also be utilised as an exercise diary for participants to record, in real time, the individual exercise sessions completed. The exercises and exercise prescription is also detailed in the app for participants to refer to. The supervising therapist (PI) has access to individual’s account providing another platform to engage with the participants and manage their exercise progression. At a minimum, participants will need to be able to attend FSH for baseline measures, at the mid-way point (three weeks), and at completion of program (6 weeks) for data collection.  Activity trackers will be utilised for both groups to quantify their average weekly activity. Participants will be provided with an activity tracker (either wrist worn or pedometer style (clothes worn)) if they do not own one themselves. They will need to be worn, at a minimum, every waking hour.

## Criteria for discontinuing or modifying allocated interventions

Exercise prescription may be modified (from the described prescription and progression) based on the participant’s response to the exercise. Intervention will be discontinued if the patient is no longer able to participate in exercise safely due to injury or a medical issue.

## Strategies to improve adherence to protocols

An accredited Physiotherapist will be responsible for each supervised exercise session at FSH to facilitate adherence and ensure safe exercise practices and techniques are adhered to.

Participants undertaking exercises at their local gym will be required to attend FSH once per week to enable appropriate progression of their exercises. Where this is not possible they will need to make contact with the supervising physiotherapist via phone to support appropriate progression of their exercise program. At a minimum, participants will need to be able to attend FSH for baseline measures, at the mid-way point (3 weeks) and at completion of program for data collection (for both study period 1 and 2). General activity will be monitored throughout the entirety of the study (including the washout period) using wearable devices. This will enable us to track participants ‘general’ activity.

## Safety Processes

Should any adverse event occur in the hospital (FSH) then the patient will be provided with first aid and then assisted to ED for assessment and treatment as necessary. Participants deemed ‘low risk’ with the APOC questionnaire and wishing to perform their exercise program at a local gym will be asked to confirm the public insurances in place, and the safety procedures followed at the gym if they suffer an adverse event. The investigator will confirm with the patient that they have reviewed these assurances prior to prescribing their program closer to home. If any adverse events occur while in the local gym then the procedure will be that the patient first seeks first aid from gym staff and then attends their local GP or ED as soon as possible. Treatment and, or adjustment of the exercise program will be made accordingly if required, as per medical review. Participants will also have access to investigators by phone to seek guidance if unsure. Potential for injury with exercise however will be minimised by having the initial exercise prescription and exercise session completed by an accredited physiotherapist. Progressions of exercises are also made under the guidance of an accredited physiotherapist by phone or the physitrack app. Further, we will ensure the gym facility to be attended has supplied adequate evidence of public liability.

## Outcome Measures

To provide greater understanding of the impact of exercise after burn injury a battery of routinely collected physical, functional and psychological outcomes, will be measured.

Primary Outcome

*TNF alpha* will be collected at baseline, mid-way and post intervention for study periods 1 and 2 (Figure 1).

Secondary Outcomes (Table 1)

The clinical outcomes to be collected include physiological (non-invasive muscle mass bioimpedance spectroscopy (40, 41)); physical (isometric grip and muscle strength (42); fitness - modified Chester Step Test [unpub data, [name], [name], [name]]); functional (QuickDASH (43), LLFI (44)); neurological (Semmes-weistein monofilament, two-point discrimination, proprioception) (45); heat response and thermoregulation (optical sensitive coherence topography, core temperature, heart rate) (46, 47); metabolome analysis (urine, skin and hair samples, plasma (multiplex of other cytokines)); microbiome analysis (skin and rectal swabs) and, quality of life (SF36 (48)). In addition, we will include a self-reported pre-study activity survey (International Physical Activity Questionnaire (IPAQ)) to ensure that the exercise levels of all recruited patients are accounted for.

**Table 1:** **Outcome measures** - All measures are collected at baseline (0 weeks), mid-way (3 weeks), post intervention (6 weeks) in study periods 1 and 2.

| **Outcome Measures** | |
| --- | --- |
| Inflammatory Biomarker | *TNF alpha* |
| Physiological and Physical | Bioimpedance Spectroscopy  Grip strength  Muscle Strength |
| Fitness/activity | Modified Chester step test,  International Physical Activity Questionnaire  Wearable fitness tracker data |
| Functional (subjective) | Quick Dash  Lower limb functional Index |
| Neurological | Semmes-weistein monofilament  Two-point discrimination  Proprioception |
| Metabolome analysis | Plasma (multiplex of other cytokines), urine, skin and hair |
| Microbiome analysis | Rectal skin swabs |
| Quality of Life | SF36 |

## Participant Timeline

Each participant (n=20) will be asked to commit to a total of 16 weeks: 6 weeks for both the intervention and control group, with a 4 week break between the two (Figure 1). We anticipate the trial (n=20) to be completed within a year. This includes recruitment, finalisation of the intervention and analysis.

Outcome measurement and blood sampling time points will be pre-intervention, at 3 weeks after commencement of intervention/control and then at 6 weeks (completion of study period one). These will then be repeated in study period two (Figure 1).

|  | **Study Period 1**  **6 weeks** | **Cross-over**  **4 week rest period** | **Study Period 2**  **6 weeks** |  |
| --- | --- | --- | --- | --- |
|  | Exercise Condition |  | Exercise Condition |  |
| Recruitment/  informed  consent |  |  |  |  |
| (over 12 months) | Control Condition |  | Control Condition |  |
|  |  |  |  |  |
|  | **Baseline** | **Outcome Measures Timeline**  **Mid-way** | **Post intervention** |  |
|  | 0 weeks | 3 weeks | 6 weeks |  |

Figure 1: Participant timeline

## Sample Size

This is a pilot and feasibility study planned to be completed in the FWF fellowship period. Current assumptions to estimate the sample size for this study, relates to data available from burn patient chronic TNF alpha levels, which were used to inform the assumptions of the calculation. A sample size of 85 patients (allowing for 15% loss to follow up) would be required to achieve 80% power to detect a change in TNF alpha, with alpha set at 5% and with an effect size of 0.3. With this pilot data, we will aim to hone the assumptions relating to the sample size to achieve definitive study outcomes and improve the strength of future grant applications to fund other components of this trial.

## Recruitment

Patients found in the SABU database, that fit the inclusion criteria will be telephoned and invited to participate in the trial. The research project will be advertised on the Fiona Wood Foundation website and face book page to capture any past burns patients not on the SABU database and children that have been burnt who are now adults. A preliminary review of SABU census to date predicted the number of patients eligible for recruitment at least one year after burn is 139. It is feasible that a significant proportion of the total of 139 patients could be contacted to offer recruitment.

# Methods: Data collection, management and analysis

## Data collection Methods

All patient demographic (gender, age, PMHx); injury or intervention (surgical procedures); and system (LOS, complications) co-variates will be recorded at recruitment and collected from the burns information management system (BIMS).

TNF alpha

A 4mL sample of blood will be collected into one Lithium Heparin (no gel, purple vile) tubes and then separated into aliquots for a) *TFN alpha* assay; and, b) other cytokine assays (UWA Burn Injury Research Unit (BIRU)). All samples will be prepared in a standardised method, separated into the required aliquots and stored in a -80^o^ freezer within 2 hours of collection. The preparation of the blood samples are as per PBMC Isolation Protocol.

The FSH Burn Unit has a suitable freezer for short term storage (< 1 week) at which time, the samples will be moved for long term storage and, or processing at UWA BIRU (inflammatory cytokine assay) to facilitate batch analyses and minimise costs. Storage of the samples at UWA BIRU are ‘in-kind’. Any blood samples not utilised will be stored, in-kind at UWA BIRU, for future transcriptomic and metabolomic analysis (within 10 years of this study).

## Data Management

The digital/soft copy raw data (outcome measures) and participant details for each patient are stored, unidentified, in a locked folder on the FSH State Adult Burns Unit portion of the secure WA health W: drive. The subfolder and file will be password protected. The passwords will be changed regularly and an automatic screen lock will be placed at 5 minutes. Fiona Stanley Hospital has a complex arrangement of firewalls and other security measures that prevent access from external sites. The participants (identified by numbers) original hard copy data sheets (including details and measures) are stored in a locked filing cabinet behind swipe access in Level 4B Burns Outpatients. The data will be stored for ten years, as required by law.

## Statistical Analysis

The primary aim of this clinical trial is to explore if a pulse of exercise influences the inflammatory biomarkers (TNFa, IL-2, IL-7 and IFNg), after burn injury.

Biomarker (serum sample) levels will be analysed using linear mixed models, including fixed effects for time, condition and their interaction, with a random effect for participant to account for the correlated observations.  Preliminary analyses will consider whether order of treatment influenced the outcome measures, and this factor will be included in the final model if appropriate. The influence of potential confounding factors (e.g. age, time post injury) will also be assessed.

Confounders such as self-motivated exercise activity will be recorded at each assessment time point to allow adjustment in the final analyses.

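### The stated mixed model has no period term and a single participant intercept, so for this two-period crossover its standard errors are miscalibrated if same-period samples are more alike

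*Protocol*

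**What the plan says.** The Introduction describes a randomised crossover: "In the second phase participants will cross over into the alternate condition". The Participant Timeline (3.7) gives "6 weeks for both the intervention and control group, with a 4 week break between the two", with 20 participants. Under Outcome Measures (3.6), TNF alpha "will be collected at baseline, mid-way and post intervention for study periods 1 and 2", so each participant gives six samples. Under Trial Design (2.3), participants "will be block randomised by year after burn to either the exercise or control condition in the first study period", in three time-since-burn groups; neither the ratio nor the block size is given.

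Statistical Analysis (4.3) states the biomarker model: "including fixed effects for time, condition and their interaction, with a random effect for participant to account for the correlated observations". It then adds: "Preliminary analyses will consider whether order of treatment influenced the outcome measures, and this factor will be included in the final model if appropriate". Period is not named. Time is not defined, but Table 1 and Figure 1 label the visits 0, 3 and 6 weeks in each period, and the Introduction says of the period 1 time points: "These will then be repeated in study period 2 at the same time points". The natural reading of time is therefore visit within period.

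**The concern.** A two-period crossover with several visits per period has three levels of variation: between participants, between periods within a participant, and between visits within a period. The stated model covers the first and last and merges the middle one into the residual. Two samples taken 3 weeks apart in one period are then treated as no more alike than two taken on either side of the break. With visit coded 0/3/6 in both periods, nothing absorbs a general difference between periods, such as season or drift with time since burn.

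Two things are at stake. The first is the width of tests and intervals. It depends on which contrast is read as the effect of exercise, and section 4.3 does not name one. The second is bias in the condition effect when a period shift meets unequal sequences. Because this is a pilot meant to refine the assumptions for a larger study, a residual that blends two variance components would also be carried into that planning.

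**Working it through.** The protocol gives no standard error or variance component on this point, so there is no figure to reproduce. The sample-size figure of 85 does not bear on it.

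**Inputs.** From the protocol: 20 participants, 2 periods, 3 visits per period, and the model in 4.3. Assumed: residual variance 1, participant-by-period variance τ² = 0, 0.5 or 1, complete data, and a 10/10 split unless stated.

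**1. What the stated model takes as its residual.** There are 120 observations. Removing 20 participant means, 2 df for visit, 1 for condition and 2 for their interaction leaves 95 df. Of these, 19 belong to participant-by-period differences, with expected mean square 1 + 3τ². The other 76 have expected mean square 1. The pooled residual is therefore 1 + (19 × 3/95)τ² = 1 + 0.6τ², which is 1.3 at τ² = 0.5 and 1.6 at τ² = 1.

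**2. Model variance against true variance.** With s² for the pooled residual:

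- Condition effect averaged over visits: model 2s²/60; true 2(τ² + 1/3)/20.
- Condition difference at week 6: model 2s²/20; true 2(τ² + 1)/20.
- Condition difference in change from week 0 to week 6: model 4s²/20; true 4/20, because τ² cancels within a period.

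| Contrast | τ² | Model variance | True variance | SE ratio | Type I error (simulated, nominal 5%) |
|---|---|---|---|---|---|
| Visit-averaged | 0.5 | 0.043 | 0.083 | 0.72 | 15.4% |
| Visit-averaged | 1 | 0.053 | 0.133 | 0.63 | 21.1% |
| Week-6 level | 0.5 | 0.130 | 0.150 | 0.93 | 6.8% |
| Week-6 level | 1 | 0.160 | 0.200 | 0.89 | 7.9% |
| Change 0 to 6 | 0.5 | 0.260 | 0.200 | 1.14 | 2.6% |
| Change 0 to 6 | 1 | 0.320 | 0.200 | 1.26 | 1.4% |

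At τ² = 0 with no period shift, every ratio is 1.00. The simulations used 20,000 trials per setting.

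**3. Serial correlation instead of τ².** With an assumed correlation of 0.5 to 0.8 per 3 weeks running on through the break (weeks 0, 3, 6, 10, 13, 16), simulation gives about 15–22% for the visit-averaged effect, 7–8% for the week-6 level and 5–7% for the change.

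**4. Period shift.** Let period 2 be shifted by δ, with n1 participants taking exercise first and n2 taking control first. The exercise-minus-control difference is θ − δ in the first sequence and θ + δ in the second. Their average is θ + δ(n2 − n1)/N, so the bias is the shift times imbalance/N:

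- 10/10: 0.
- 11/9: 2/20 = 0.10δ.
- 12/8: 4/20 = 0.20δ.
- If 15% of 20 (3 people) were lost, 17 would remain: 9/8 gives 1/17 = 0.06δ and 10/7 gives 3/17 = 0.18δ.

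A constant δ is the same at weeks 0 and 6, so it cancels from the change contrast at any split. A period difference in the 0-to-6-week trend does not cancel: 0.10 or 0.20 of its size enters the change contrast at 11/9 or 12/8.

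At 10/10, an omitted shift of 1 residual SD adds 120 × 0.5²/95 = 0.32 to the residual. The ratio becomes √1.32 = 1.15, and simulated type I error is about 2.5% at τ² = 0.

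**5. Which part of the remedy does what (τ² = 0.5).** Adding only a period main effect leaves type I error at about 15–16% for the visit-averaged effect and 2.5–4% for the change. At 12/8 it also leaves the 0.20 trend leak in the change contrast. Period-by-visit removes that leak. Comparing within-participant period differences between sequences (20 − 2 = 18 df) gives 4.7–5.3% for all three contrasts at 10/10 and 12/8, at τ² = 0.5 and 1, with bias about 0.

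**The case against.** The strongest reply is that section 4.3 already provides for order of treatment. In a two-sequence, two-period design, order-by-condition is equivalent to period, so an order analysis containing that interaction would cover a period shift. The text, however, speaks of order as a factor. A sequence main effect varies only between participants and does not remove a period shift. Inclusion also depends on a preliminary look at about 20 people, which has little power. The sentence is a partial and conditional safeguard, and it does not touch the covariance.

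Second, time is undefined. If it meant all six occasions, period would be absorbed. Table 1 and Figure 1 point the other way, and the single intercept would remain in either case.

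Third, covariance structure and degrees of freedom are often left to a SAP. That would be decisive if the protocol were silent, but it states the random structure.

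Three stronger readings do not hold:

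- A reader might infer that the standard errors are simply wrong. That needs participant-by-period variance, serial correlation or an omitted period shift, and the protocol documents none of these.
- A reader might take 15–21% as the false-positive rate of the exercise test. That rate belongs to an average that includes the pre-intervention visit. Each period has its own baseline, so the natural test is time-by-condition, which is conservative or near nominal.
- A reader might infer that any dropout turns a period shift into a treatment effect. The leak needs unequal sequences, and a constant shift never reaches the change contrast.

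Batch assay (4.1) may also lessen assay drift. Learning on the strength or step tests is not relevant to a model stated for biomarkers.

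**Conclusion.** The point holds in a conditional form. As written, the model does not match a two-period crossover with three visits per period, and its calibration depends on variances that the protocol does not give. At an assumed participant-by-period variance of 0.5 to 1 times the residual, type I error is about 15–21% for the visit-averaged condition effect, 7–8% for the week-6 level and 1–3% for the change. If all three sources of departure are zero, there is no error.

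For the contrast most analysts would choose, the likely cost is lost precision, or near-nominal error under serial correlation, rather than false positives. The anti-conservative contrast remains open only because 4.3 does not say which one tests exercise. Period bias is shift × imbalance/N for level contrasts. For the change contrast only a period difference in trend matters, and only when sequences are unequal. Expressing this bias as a share of the 0.3 effect size in Sample Size (3.8) is not supported, because that section does not say what the 0.3 is standardised by.

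The model should be changed, since the correction is nearly free, but the pilot is not invalidated.

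**What to change.** In section 4.3:

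- Define time as visit within period (0, 3, 6 weeks).
- Include period and period-by-visit as fixed effects in every case, whatever the preliminary order analysis shows.
- Add a participant-within-period random effect alongside the participant effect, or an equivalent within-period covariance, with small-sample degrees of freedom such as Kenward-Roger. The covariance form also allows for serial correlation between visits.
- Name the condition-by-visit contrast at week 6, that is, the change from that period's baseline, as the test of exercise.

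The cost is a few lines of text and code. The model gains three fixed parameters (one for period, two for period-by-visit) and at least one variance parameter, which is a modest burden at n=20. An unstructured within-period covariance needs more and may be hard to fit if data are missing. The pilot would then also report the participant-by-period and residual variances separately, which the planning of the larger study needs.
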